### Study design

Randomised, controlled, evaluator-blinded, prospective parallel-group trial based on Consolidated Standards of Reporting Trials (CONSORT) Statement for Randomised Trials of Non-Pharmacologic Treatment [49].

### Participants

Children were eligible to participate if they met the following criteria:

### Exclusion Criteria

Children who otherwise met the inclusion criteria were excluded if they had:

• Congenital quadriplegic or diplegic cerebral palsy.

• Previous BoNT-A injections in the upper limb in the past 12 months.

• Prior upper limb surgery (i.e. tendon transfer/tendon lengthening).

• Existing treatments that are not compatible with those those included in the study treatment package.

There were no criteria relating to exclusion of children with mother tongue other than English, presence of co-morbidity or socio-economic status.

### Recruitment

Potential participants were identified from the Physical Rehabilitation Clinic of a major paediatric metropolitan hospital. In addition, postal and email advertising were sent to local medical practitioners and paediatric therapy networks in metropolitan Melbourne. Potential participants were screened by the chief investigator ([name]) to determine eligibility. Children eligible for inclusion were then assessed by an experienced rehabilitation specialist for suitability for upper limb BoNT-A injection ([name]). Suitable children were then invited to participate in the RCT and informed consent obtained for the participation of the child and the child's parent prior to enrolment in the RCT.

### Procedure

The RCT was approved by the Ethics Committee of both Southern Health and La Trobe University. The trial is registered with the Australian New Zealand Clinical Trials Registry (ACTRN12605000002684) [50]. Data was collected from August 2003 until May 2009.

### Reliability training for assessment and scoring of outcome measures

Prior to commencement of the RCT, two highly experienced paediatric therapists (one occupational therapist, one physiotherapist) were trained in the administration of all outcome measures. A manual was developed for both therapists to ensure consistency in measurement over the recruitment period. The same occupational therapist collected data for the Assisting Hand Assessment, Quality of Upper Extremity Skills Test, Pediatric Evaluation of Disability Inventory, Pediatric Motor Activity Log, Canadian Occupational Performance Measure and Goal Attainment Scaling for the entire recruitment period. Two physiotherapists collected data for the modified Ashworth and modified Tardieu Scales. Scoring of the Assisting Hand Assessment was undertaken by the assessment developers. The Quality of Upper Extremity Skills Test was scored by a highly experienced paediatric occupational therapist who had significant experience in the assessment and treatment of children following upper limb BoNT-A injections.

## Randomisation

### Sequence generation

Children were block randomised into pairs matched by age (± 6 months) using a computer generated set of random numbers.

### Allocation Concealment

A set of random numbers was used to create an allocation sequence which was contained in individual opaque envelopes for use by the chief investigator ([name]). As children were recruited, the next envelope in the sequence was opened and the child assigned to the stated group.

### Implementation

All randomisation, sequence generation, and preparation of group allocation materials were performed by a third party (the Monash Institute of Health Services Research) who had no direct contact with the clinical aspects of the trial. The master list of random numbers was located in locked cabinets at the Institute and only accessible at completion of the RCT for analysis.

### Blinding

Due to the overt nature of the interventions, children, their parents and the treating therapist were not blinded to group assignment, however, children and parents were blind to the RCT hypotheses. Outcome measures were administered by a therapist blind to group assignment and scored by different assessors who were blind to group allocation. The Assisting Hand Assessment and Quality of Upper Extremity Skills Test was videotaped, randomised and scored by assessors blind to group allocation and order of assessment.

### Sample Size

Sample size estimates were based on projected treatment effect on the primary outcome measure, the Assisting Hand Assessment. In 2005, the authors suggested that a change of more than 5 raw score points may represent a clinically meaningful difference on the Assisting Hand Assessment ([name], personal communication). This was the equivalent to a change in 2.6 logits. Calculation for fractions of logits undertaken by a statistician indicated that in order to detect a change of 2.6 logits a minimum sample size of 17 per group was required. As the RCT design involves a two-group design, a total sample size of 34 was required to provide 80% power to detect clinically meaningful change between groups. Therefore, the study aimed to recruit 40 children to allow for a 10-12% drop-out rate.

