### Secondary objectives

A. To compare the effect of modified CIMT versus bimanual occupational therapy (BOT) on secondary outcomes relating to: the performance of activities of daily living; the quality of upper limb movement; occupational performance; individual goal achievement; and frequency of use of the affected upper limb of children with hemiplegic cerebral palsy following upper limb BoNT-A injection.

#### Hypothesis 3

Modified CIMT is more effective than conventional BOT in improving performance of activities of daily living, quality of upper limb movement, occupational performance, individual goal achievement and frequency of use of the affected upper limb in children with hemiplegic cerebral palsy following upper limb BoNT-A injection.

B. To evaluate the clinical significance of change identified on the primary outcome, the Assisting Hand Assessment.

#### Hypothesis 4

That changes on the Assisting Hand Assessment associated with intervention are of a clinically significant magnitude. Clinical significance was defined as a change score of more than 5 raw score points (2.6 logits) on the AHA ([name], personal communication).

C. To evaluate the impact of age and actual treatment dosage on the primary outcome, the Assisting Hand Assessment.

#### Hypothesis 5

Younger children (irrespective of treatment type) will show greater improvement in bimanual performance following uni-manual or bimanual therapy and upper limb BoNT-A injection.

#### Hypothesis 6

Children who undertake treatment of greatest intensity (irrespective of treatment type) will show greater improvement in bimanual performance.

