### Primary Outcome

The primary outcome measure was the Assisting Hand Assessment (AHA) [51]. The administration of the AHA (Small Kids English version 4.4) was videotaped. The AHA is a standardized, criterion-referenced test for use with children aged 18 months to 12 years, who have a unilateral upper limb impairment [51]. It aims to measure how effectively a child uses their affected hand in bimanual play activities using 22 items. Unlike most other upper limb assessments for children with cerebral palsy, the AHA attempts to capture a child's typical performance when performing tasks rather than their best effort or "capacity" [51]. Change on the AHA is therefore more likely to reflect change in the child's upper limb use across multiple environments.

The AHA is conducted by video observation of the child involved in a 10-15 minute play session using the AHA test kit with specific toys. The twenty-two items defining different actions are then scored on a 4-point scale rating the quality of the performance. Four being effective, 3 somewhat effective, 2 ineffective and 1 indicating the child does not perform the action. The sum of raw scores (sum score) varies between 22 (low ability) to 88 points (high ability). Raw scores are converted to scaled scores ranging from 0 to 100. Using a computer generated logarithmic transformation, ordinal data are then converted to equal intervals in the unit logits [51]. The range of the AHA scale is -10.18 to +8.70 logits. Logit scores will be used in the analysis of data for this RCT.

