The psychometric properties of the AHA have been described in several studies [51-54]. Using Rasch measurement analysis, validity and aspects of reliability were evaluated, with excellent results. There is strong evidence that AHA items measure a uni-dimensional construct with 95% of items fitting Rasch assumptions. Person response validity demonstrated that 97% of person's responses fitted the model. A person separation index of 6.16 demonstrated a very good ability to distinguish children of different ability levels [51,52]. A standard error mean of 0.28 (range 0.26-0.32) revealed the precision and reliability of the item measures [51]. More recently, reliability of the Small Kids AHA was found to be excellent with Intraclass Coefficients (ICC's) of 0.97 (20 raters) to 0.98 (2 raters) for interrater and for the intrarater 0.99 [53]. The same version also demonstrated excellent test-retest reliability (ICC 0.99). The Smallest Detectable Difference (SDD) over time indicated that a change in AHA scores from one test session to the next must be 3.89 sum scores (0.97 logits) or more to be considered a true change with 95% probability [54]. The AHA was initially designed for evaluation within a trial of CIMT [8] where it demonstrated responsiveness to change. Since then, studies evaluating HABIT [31,48] have also shown some change in the treatment group compared to the control group, providing evidence that the AHA was also responsive to change following bimanual intervention.

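### Five AHA raw points are equated with 2.6 logits, about twice what the protocol's own scale figures give, so the 80% power claim and the Hypothesis 4 threshold are wrong as written

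*Protocol article*

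**What the plan says.** The Sample Size section reports advice that "a change of more than 5 raw score points may represent a clinically meaningful difference on the Assisting Hand Assessment" and continues: "This was the equivalent to a change in 2.6 logits". From there, "in order to detect a change of 2.6 logits a minimum sample size of 17 per group was required", and "a total sample size of 34 was required to provide 80% power to detect clinically meaningful change between groups". The recruitment target of 40 allows for drop-out.

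Hypothesis 4, under Secondary objectives, repeats the equivalence and defines clinical significance as "a change score of more than 5 raw score points (2.6 logits) on the AHA".

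The Primary Outcome section gives two other links between the raw and logit scales. The sum score runs from 22 to 88, and "The range of the AHA scale is -10.18 to +8.70 logits". On measurement error, "a change in AHA scores from one test session to the next must be 3.89 sum scores (0.97 logits) or more" to count as a true change. The same section fixes logits as the analysis scale.

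**The concern.** The equivalence implies 2.6 / 5 = 0.52 logits per raw point, which neither of the other two figures supports. Beside the smallest detectable difference the conflict is plain. If 3.89 points are 0.97 logits and 5 points are 2.6 logits, the last 1.11 points must add 1.63 logits. That is 1.47 per point, about six times the rate of the first 3.89.

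Three things depend on it:

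- **Power.** The trial is said to have 80% power for a clinically meaningful difference, defined as more than 5 raw points, but the calculation used a logit difference about twice that size.
- **Hypothesis 4.** One definition holds two thresholds. In mid-scale, a change of about 6 to 9 raw points meets the raw rule and fails the logit rule. Since analysis is in logits, the stricter figure is likely to be applied, and meaningful gains could be reported as not clinically significant.
- **Interpretation.** A null result for Hypothesis 1 could be read as an adequately powered exclusion of a 5-point difference.

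**Working it through.** **Inputs.** From Sample Size: 5 raw points, 2.6 logits, 17 per group, 80% power. From Primary Outcome: sum score 22 to 88, logit range -10.18 to +8.70, and 3.89 sum scores = 0.97 logits. The SD, alpha and sidedness are not given for the sample size. I assume a two-sided 5% test and vary this below.

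**1. Raw-to-logit conversion from the article's own figures**

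| Anchor | Logits per point | 5 points | 2.6 logits | 2.6 / (5 points) |
|---|---|---|---|---|
| Full range | 18.88 / 66 = 0.286 | 1.43 logits | 9.1 points | 1.8 |
| Smallest detectable difference | 0.97 / 3.89 = 0.249 | 1.25 logits | 10.4 points | 2.1 |

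The 0 to 100 scaled score does not help. If it is linear in logits, 5 scaled points are 5 × 18.88 / 100 = 0.94 logits, further still from 2.6.

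**2. The plan's own sample size.** Without an SD, 17 per group cannot be reproduced, only back-solved. A two-sample t-test with 17 per group, 80% power and two-sided 5% needs a standardised difference of d = 0.991, so SD = 2.6 / 0.991 = 2.62 logits (2.71 by the normal approximation). At one-sided 5% the implied SD is 2.98 (t) or 3.05 (normal). The drop-out step is consistent: 34 / 0.90 and 34 / 0.88 round up to 38 and 39, within the target of 40.

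**3. Power for 5 raw points, with that implied SD and no covariate adjustment**

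| Difference | d = difference / 2.62 | 17 per group | 20 per group | Needed per group for 80% |
|---|---|---|---|---|
| 1.25 logits | 0.48 | 27% | 31% | 71 to 74 |
| 1.43 logits | 0.55 | 34% | 39% | 54 to 57 |

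The last column spans the t and normal calculations. A one-sided 5% test gives 33% to 39% at 17 per group. Conversely, 17 per group would give 80% power for 5 points only if the SD were about 1.26 to 1.49 logits. With an SD of 1.5, the 2.6-logit difference would have needed only 6 or 7 per group.

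**4. Crediting the planned ANCOVA.** If 2.62 is the unadjusted SD and the baseline-outcome correlation is r, the residual SD is 2.62 × √(1 − r²). Power at 17 per group for 1.25 and 1.43 logits:

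| Assumed r | Residual SD | 1.25 logits | 1.43 logits |
|---|---|---|---|
| 0.5 | 2.27 | 34% | 43% |
| 0.8 | 1.57 | 61% | 73% |
| 0.9 | 1.14 | 87% | 94% |

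Power reaches 80% at r of about 0.88 for 1.25 logits and 0.84 for 1.43 logits.

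**The case against.** The strongest reply has four parts.

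- **The power for 2.6 logits is not refuted.** With no SD or alpha stated, that claim can be neither reproduced nor rejected. If 2.6 logits was the intended threshold, the sample size may stand and the raw figure is the slip. This is right: the article does not show which figure was meant. But the article claims 80% power for the difference it defines as more than 5 raw points, and that fails unless the equivalence holds.
- **The planned analysis is ANCOVA, not a t-test.** Adjusted power could reach 80% for 5 points if the correlation is high, and the reported test-retest ICC of 0.99 makes a high correlation plausible. That ICC is not a correlation over one to six months of treatment, however. If the statistician's SD was already a change or residual SD, crediting ANCOVA would count the adjustment twice. The true power for 5 points is therefore unknown, which is why a range is shown. It does not restore the stated basis for 80%.
- **The conversion is not linear, and the rule is more than 5.** A Rasch scale is expected to be steeper near its ends, so 1.25 to 1.43 is an estimate. But 2.6 logits for 5 points needs about twice the slope of either anchor, and the article states the equivalence without restriction. On an integer score the smallest qualifying change is 6 points, about 1.50 to 1.72 logits. The ratio then falls to 1.5 to 1.7 and unadjusted power at 17 per group rises to about 36% to 46%. The mismatch shrinks but remains.
- **The consequences are limited.** Hypothesis 4 is secondary, its test compares the magnitude of effect with the criterion rather than explicitly classifying each child, and group differences come with 95% confidence intervals. This lowers the risk of over-reading a null result, but any comparison with the criterion still has two possible answers.

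**Conclusion.** The concern holds. The article's stated equivalence is 1.8 to 2.1 times what its own scale figures give, and 2.6 logits corresponds to about 9 to 10 raw points. The conflict over the Hypothesis 4 threshold depends on no assumption about SD, alpha or correlation.

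The claim of 80% power for a 5-point difference has no valid basis as written. How far actual power falls short depends on quantities the article does not give. It is 27% to 34% at 17 per group under an unadjusted two-sided 5% t-test with the back-solved SD, and anywhere from 34% to 94% under ANCOVA with assumed correlations of 0.5 to 0.9.

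**What to change.** Read the logit value of a 5-point change from the AHA raw-to-logit conversion table; mid-scale it should be near 1.25 to 1.43. If 5 raw points is the intended criterion, replace 2.6 logits with that value in both Sample Size and Hypothesis 4, and apply one criterion on one scale. Restate the power of 17 per group for that difference under the planned ANCOVA, naming the SD, alpha, sidedness and baseline correlation used.

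If 2.6 logits was intended, correct the raw figure in both places and say that the trial is powered only for about 9 to 10 raw points.

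Either way the cost is a wording change and one recalculation. Recruitment and follow-up are complete and analysis is under way, so no patients are added, but the criterion should be settled before Hypothesis 4 is assessed. If the 5-point criterion is kept, the stated power is likely to be less favourable.

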### Outcome measures

Outcomes measures were completed on four occasions: baseline (1 to 2 weeks prior to injection), and at 1, 3 and 6 months after injection. Outcomes included measures from across the International Classification of Functioning, Disability and Health (ICF) [18] spectrum and involved a combination of investigator observed and parent report measures (See Table 1). This enabled analysis of the impact of intervention across the body function and activity domains.

**Table 1 T1:** Outcomes classified according to International Classification of Functioning, Disability and Health (ICF)

Body Function	Activity	
	
	Capacity	Performance
modified Tardieu Scale (MTS), modified Ashworth Scale (MAS), Quality of Upper Extremity Skills Test (QUEST; dissociated movement subscale)	Quality of Upper Extremity Skills Test (grasps subscale)	Assisting Hand Assessment (AHA), Canadian Occupational Performance Measure (COPM), Goal Attainment Scaling (GAS), Pediatric Evaluation of Disability Inventory (PEDI), Pediatric Motor Activity Log (PMAL)

The effects of upper limb BoNT-A injection in both groups were monitored using measures of muscle spasticity and muscle tone including the Modified Ashworth Scale (MAS) and Modified Tardieu Scale (MTS).

### Primary Outcome

The primary outcome measure was the Assisting Hand Assessment (AHA) [51]. The administration of the AHA (Small Kids English version 4.4) was videotaped. The AHA is a standardized, criterion-referenced test for use with children aged 18 months to 12 years, who have a unilateral upper limb impairment [51]. It aims to measure how effectively a child uses their affected hand in bimanual play activities using 22 items. Unlike most other upper limb assessments for children with cerebral palsy, the AHA attempts to capture a child's typical performance when performing tasks rather than their best effort or "capacity" [51]. Change on the AHA is therefore more likely to reflect change in the child's upper limb use across multiple environments.

The AHA is conducted by video observation of the child involved in a 10-15 minute play session using the AHA test kit with specific toys. The twenty-two items defining different actions are then scored on a 4-point scale rating the quality of the performance. Four being effective, 3 somewhat effective, 2 ineffective and 1 indicating the child does not perform the action. The sum of raw scores (sum score) varies between 22 (low ability) to 88 points (high ability). Raw scores are converted to scaled scores ranging from 0 to 100. Using a computer generated logarithmic transformation, ordinal data are then converted to equal intervals in the unit logits [51]. The range of the AHA scale is -10.18 to +8.70 logits. Logit scores will be used in the analysis of data for this RCT.

The psychometric properties of the AHA have been described in several studies [51-54]. Using Rasch measurement analysis, validity and aspects of reliability were evaluated, with excellent results. There is strong evidence that AHA items measure a uni-dimensional construct with 95% of items fitting Rasch assumptions. Person response validity demonstrated that 97% of person's responses fitted the model. A person separation index of 6.16 demonstrated a very good ability to distinguish children of different ability levels [51,52]. A standard error mean of 0.28 (range 0.26-0.32) revealed the precision and reliability of the item measures [51]. More recently, reliability of the Small Kids AHA was found to be excellent with Intraclass Coefficients (ICC's) of 0.97 (20 raters) to 0.98 (2 raters) for interrater and for the intrarater 0.99 [53]. The same version also demonstrated excellent test-retest reliability (ICC 0.99). The Smallest Detectable Difference (SDD) over time indicated that a change in AHA scores from one test session to the next must be 3.89 sum scores (0.97 logits) or more to be considered a true change with 95% probability [54]. The AHA was initially designed for evaluation within a trial of CIMT [8] where it demonstrated responsiveness to change. Since then, studies evaluating HABIT [31,48] have also shown some change in the treatment group compared to the control group, providing evidence that the AHA was also responsive to change following bimanual intervention.

### Monitoring responses to Botulinum toxin-A injection

The Modified Ashworth Scale (MAS) is a 6-point, criterion referenced ordinal scale deigned to measure the resistance that is encountered when a limb is moved passively [55]. Scores range from 0 (no increase in muscle tone) to 4 (rigid). Movements assessed included: shoulder abduction and flexion; elbow extension and flexion; forearm supination and pronation; wrist extension and flexion; ulnar and radial deviation and thumb abduction.

The MAS has often been described in the literature as a measure of spasticity [55,56], however since muscle resistance in children with cerebral palsy is due to a combination of factors, only one of which is spasticity, the MAS is considered to have poor validity for spasticity evaluation [57]. Further, as there is no reference to the velocity of limb movement during examination, a central criterion in defining spasticity [3], the MAS is considered a measure of muscle tone. Following a review of papers across a broad range of diagnostic groups, Morris [58] estimated intra-rater reliability to be between 0.55 to 0.83 and 0.45 to 0.84 for inter-rater reliability. These estimations have been supported in recent studies in children with cerebral palsy where inter-rater reliability has been described as low [59,60]. To improve the reliability of using the MAS in this RCT, two physiotherapists, independent to the intervention component of the trial and experienced in administration and scoring of the MAS performed all assessments at a slow velocity. The MAS has demonstrated change in children following upper limb injection of BoNT-A combined with occupational therapy [24,25,61].

The modified Tardieu scale (MTS) was adapted from the original scale developed by Tardieu and colleagues [62]. The MTS grades the quality of the reaction of the muscle to passive stretch and measures the dynamic component of muscle spasticity [63]. This measure of spasticity is obtained when a joint is moved as fast as possible through its range of movement (V3 velocity) and the angle of "catch" elicited is measured using a goniometer. This is called R1. The difference between the angle of "catch" (R1) and the full passive range of movement (R2) reflects the potential range available in the joint if spasticity is eliminated [9,63]. The quality of the muscle reaction (resistance) is also rated when obtaining the R2 measurement, from 0 (no resistance through the course of the passive movement) to 5 (joint immovable).

In this RCT, administration of the MTS was jointly performed by an occupational therapist and physiotherapist both blinded to group assignment. Movements measured included: shoulder abduction and flexion; elbow extension and flexion; forearm supination and pronation; wrist extension and flexion; ulnar and radial deviation and thumb abduction. The velocity used to determine the angle of catch was V3 (as fast as possible), as recommended by Morris [58]. The MTS scale has demonstrated sensitivity to change when measuring spasticity following BoNT-A injection in the upper limb [24] and lower limb [63] in children with cerebral palsy. Despite this reported sensitivity, the MTS has demonstrated poor reliability as a measure of elbow flexor spasticity in children with cerebral palsy with large inter-sessional variation and difficulty in applying standardised velocities [64]. The MTS however, is still considered the only clinically valid measure of spasticity currently available [57,65]. To improve reliability of the MTS in this RCT, the same blinded raters (one occupational therapist, two physiotherapists) were used for each assessment occasion for each child.

